### Sample size calculation

In this study, two primary endpoints are specified. If the superiority of Yokukansan over placebo for either endpoint is confirmed, the drug would be considered to be effective. Therefore, considering the Bonferroni adjustment for multiplicity, a two-sided significance level of 2.5% is used for each endpoint. Regarding the incidence of postoperative delirium—one of the primary endpoints—a previous meta-analysis reported that antipsychotics reduced the incidence of delirium by 50% compared to placebo [44]. The effect of Yokukansan against BPSD, which is thought to be a condition similar to delirium, has repeatedly been demonstrated in randomized controlled trials and is non-inferior to that of antipsychotics [27, 30–34], so we anticipated obtaining the same results against postoperative delirium. Therefore, we estimated an effect size for Yokukansan of 0.5 for postoperative delirium. Yokukansan has few side effects, and if we can show that its effects are comparable to those of antipsychotics, the results may change current clinical practice, in which antipsychotics are generally used as a first line pharmacotherapy to prevent postoperative delirium. Based on an observational study that we performed using exactly the same inclusion and exclusion criteria at the same hospital [5], we estimated the incidence of delirium at 40% in the placebo group and 20% in the Yokukansan group. Given a two-sided significance level of 2.5% and a statistical power of 80%, this indicates that 99 subjects per group are necessary. As for the change in preoperative anxiety, the minimum clinically meaningful difference in anxiety score was shown in a previous study to be 1.32 points, although in that case the subjects were patients with chronic obstructive lung disease [45]. Therefore, in this study we assume a between-group difference in the mean change in preoperative anxiety of 1.5 points. Assuming a 3-point standard deviation in the preoperative anxiety score, a two-sided significance level of 2.5%, and a statistical power of 80% based on the results of an observational study conducted at the National Cancer Center Hospital [13], 78 subjects per group are necessary. Considering the above and speculating that some subjects may later be found to be ineligible or may withdraw from the study, the planned number of registered subjects was determined to be 110 per group, or 220 in total.

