## Background

Patients with cancer experience various psychiatric symptoms during the perioperative period. Anxiety not only lowers treatment compliance by impairing cancer patients’ decision-making ability [1], but it also exacerbates cancer symptoms, leading to reduced quality of life [2]. During the perioperative period, anxiety has also been reported to prolong postoperative pain [3], affect endocrine and immune functions, and influence the progression and long-term prognosis of cancer [4]. An observational study previously conducted at our hospital showed that preoperative anxiety occurred in approximately 15% of cancer patients [5]. Hence, we consider that reducing preoperative anxiety is an important goal of cancer treatment in general.

Delirium is a psychiatric disorder characterized by acute impairment of consciousness and lack of attention [6]. Postoperative delirium refers to delirium that occurs after patients recover from anesthesia, typically within 2 or 3 days after the operation [7–10]. Patients with postoperative delirium experience not only increased rates of respiratory infection and complications associated with immobility and prolongation of hospitalization, but also long-term adverse effects including increased mortality rate [11–13] and impaired cognitive function [14–16]. In the aforementioned observational study, postoperative delirium occurred in approximately 32% of cancer patients [5].

Perioperative psychiatric symptoms should be appropriately assessed, treated, and prevented. However, when used in patients with impaired metabolic capacity, benzodiazepines, which are common therapeutic agents for anxiety, may have long-lasting effects or cause muscle relaxation, resulting in falls. They are also considered to induce delirium when used in patients with cerebral vulnerability, including elderly patients and patients with dementia [17–21]. The antipsychotic agents used for the treatment of postoperative delirium may cause dose-dependent over-sedation or serious adverse drug reactions that include extrapyramidal symptoms and long QT syndrome. Moreover, antipsychotic agents have been reported to increase mortality risk when used in elderly patients with dementia and are often difficult to use in the treatment of elderly patients or patients with heart disease [22–24].

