## Discussion

Preoperative anxiety and postoperative delirium affect both short- and long-term prognoses in patients with cancer and therefore need to be appropriately assessed, treated, and prevented. However, neither preventive nor therapeutic methods have been established for these conditions.

The present study is the first randomized, double-blind, placebo-controlled study conducted to clarify the effects of a Japanese herbal medicine, Yokukansan, for the prevention and treatment of perioperative psychiatric symptoms in patients with cancer. Although Yokukansan has already been approved for anxiety, existing findings are insufficient to allow a clear conclusion regarding its efficacy in preoperative conditions in particular. There are no standard therapeutic regimens for preoperative anxiety or postoperative delirium in cancer patients. For these reasons, if the present study can clarify the therapeutic effect of Yokukansan on preoperative anxiety, its preventive effect on postoperative delirium, and its safety in cancer patients, it will greatly contribute to the establishment of standard therapies for perioperative psychiatric symptoms in this population, leading to the provision of safer medical care with higher compliance. However, if the effect of Yokukansan is not verified in this study, the lack of clear evidence will suggest that continued use of this agent in daily practice can be stopped.

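### The delirium sample size bases a 40% placebo rate on an observational study that the same article reports at about 32%; if 32% holds and the planned halving is kept, power is about 66% to 71%, not 80%.

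*Protocol article*

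**What the plan says.** The protocol article gives two figures for delirium and ties both to reference 5.

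- Background: "In the aforementioned observational study, postoperative delirium occurred in approximately 32% of cancer patients [5".
- Sample size calculation: "Based on an observational study that we performed using exactly the same inclusion and exclusion criteria at the same hospital [5", after which "we estimated the incidence of delirium at 40% in the placebo group and 20% in the Yokukansan group".

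The treatment effect is set as a ratio. The sample size section notes that "a previous meta-analysis reported that antipsychotics reduced the incidence of delirium by 50% compared to placebo [44" and then states that "we estimated an effect size for Yokukansan of 0.5 for postoperative delirium". The 20% treated rate is therefore half of the assumed 40%.

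With two primary endpoints and a Bonferroni split, "a two-sided significance level of 2.5% is used for each endpoint". The result is: "Given a two-sided significance level of 2.5% and a statistical power of 80%, this indicates that 99 subjects per group are necessary". Registration is then raised to 110 per group to allow for ineligible subjects and withdrawals, with no loss rate stated.

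**The concern.** One study cannot be both the source of a 40% planning rate and a report of about 32% without some explanation. The article offers none: no subgroup, no other definition of delirium, no different assessment window. The most natural explanation would be that the trial enrols a higher-risk population than the observational study did. The statement that the eligibility criteria were identical makes that hard to invoke.

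The delirium endpoint needs the larger sample (99 per group, against 78 for anxiety), so it sets the size of the trial. A lower control rate with the same relative effect gives a smaller absolute difference and less power. If 32% is nearer the truth, a drug that really halves delirium would miss significance on this endpoint about one time in three, and not one time in five as the stated power implies.

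**Working it through.** **Inputs, all from the article.** Two-sided level 0.025 per endpoint; power 80%; placebo and treated rates 40% and 20%; relative effect 0.5; 99 per group required and 110 per group registered (Sample size calculation). Chi-square test of proportions (Statistical analysis). Rate of about 32% in reference 5 (Background).

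**Formula.** Pooled-variance comparison of two proportions without continuity correction, with p̄ = (p1 + p2)/2, A = √[2p̄(1 − p̄)] and B = √[p1(1 − p1) + p2(1 − p2)]:

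- n per group = (2.2414·A + 0.8416·B)² / (p1 − p2)²
- power = Φ{[(p1 − p2)·√n − 2.2414·A] / B}

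Here 2.2414 is the normal quantile for two-sided 2.5% and 0.8416 the quantile for 80% power.

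**Step 1: reproduce the plan's figure (40% versus 20%).** p̄ = 0.30, A = √0.42 = 0.6481, B = √0.40 = 0.6325. Then n = (1.4526 + 0.5323)² / 0.04 = 98.5, so 99 per group, with power 80.2%. The stated 99 is right for its inputs.

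**Step 2: the Background rate with the plan's own halving (32% versus 16%).** p̄ = 0.24, A = √0.3648 = 0.6040, B = √0.3520 = 0.5933.

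- 99 per group: (0.16 × 9.9499 − 1.3538) / 0.5933 = 0.401, power 65.6%.
- 110 per group: (0.16 × 10.4881 − 1.3538) / 0.5933 = 0.547, power 70.8%.
- For 80% power: n = (1.3538 + 0.4993)² / 0.0256 = 134.1, so 135 per group.

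Exact enumeration of the uncorrected chi-square test gives 65.9% and 71.6%, so the approximation is adequate.

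**Step 3: sensitivity at 99 per group.**

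| Placebo | Treated | What is kept | Power |
|---|---|---|---|
| 31% | 15.5% | halving | 63.5% |
| 32% | 16% | halving | 65.6% |
| 33% | 16.5% | halving | 67.6% |
| 32% | 12% | 20-point difference | 88% |
| 32% | 20% | treated rate | 37% |

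Rounding in the approximate 32% hardly matters. What is carried over matters a great deal. The article derives the effect as a ratio, so halving is the reading it supports; 32% versus 12% would need a relative risk of 12/32 = 0.375, for which it gives no basis.

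**Step 4: effect detectable with 80% power at a 32% control rate.** Solving the power formula for the treated rate gives 13.7% at 99 per group (13.7/32, relative risk 0.43) and 14.5% at 110 per group (14.5/32, relative risk 0.45).

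**The case against.** The strongest reply is that the 40% is presented as a planning estimate informed by the study, not as a figure quoted from it. Reference 5 is not at hand, so its denominator and delirium definition cannot be checked, and it may contain a sound basis for 40%. This stands to the extent that 32% is not shown to be the right placebo rate. It does not remove the need to explain the difference.

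It can also be said that 110 per group are planned and that the Statistical analysis section counts all registered subjects in the efficacy analysis. But the surplus over 99 is there to absorb losses, the delirium proportion is taken among patients whose planned surgery is completed, and missing data are not imputed. So 71% is a ceiling, while 66% is the like-for-like comparison with the stated 80%, which is attached to 99.

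A reader might infer three stronger points, and the article supports none of them.

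- **That the trial's true power is 66%.** The figure is conditional on 32%, on halving and on 99 evaluable per group, and it concerns one endpoint. The trial succeeds on either. Under the plan's own anxiety assumptions (1.5 points, SD 3) the anxiety comparison has about 90% power at 99 per group. The chance of at least one success is then about 1 − (1 − 0.895)(1 − 0.656) = 96%, if the two endpoints are treated as independent.
- **That a missed delirium endpoint would by itself lead to the drug being abandoned.** The Discussion does say that "the lack of clear evidence will suggest that continued use of this agent in daily practice can be stopped", but this follows from the drug's effect not being verified in the study, and success on either endpoint counts as verification.
- **That a null delirium result would be uninformative.** With no observed difference at a 32% rate, the 97.5% confidence interval has a half-width of 2.2414 × √(2 × 0.32 × 0.68 / n), which is 14.9 points at 99 per group and 14.1 at 110. That would exclude the 16-point halving. Smaller benefits would stay open, but the article sets no threshold for a worthwhile effect.

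**Conclusion.** The concern holds as an unreconciled planning assumption. The sample size section and the Background give 40% and about 32% on the strength of one study, without explanation. The calculation itself is correct for 40% versus 20%.

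Under 32% versus 16%, the delirium comparison has about 66% power with 99 evaluable per group and at most about 71% with 110, against the stated 80%. This rests on the Background rate being the applicable one and on the plan's relative reduction carrying over unchanged. It is a statement about the delirium endpoint only, and it matters most if the drug acts on delirium but not on anxiety.

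**What to change.** Reconcile the Background and the sample size section in one of two ways.

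1. State where 40% comes from in reference 5 (for example a defined subgroup or another delirium definition, if that is the source) and why it suits this population better than 32%.
2. Otherwise, restate the delirium power as about 66% (99 evaluable per group) to 71% (110 per group) under 32% versus 16%. Give the treated rate detectable with 80% power at a 32% control rate: about 13.7% at 99 per group and 14.5% at 110. Say that this power applies to the delirium endpoint alone.

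The cost is a few sentences and, under the second option, a less favourable stated power. No extra patients are needed, and the planned analysis does not change. A look at the blinded pooled delirium rate would not settle the matter, because a pooled 24% fits 32% versus 16% as well as 24% in both groups.

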### Statistical analysis

The analysis sets for efficacy and safety include all registered subjects. The mean change in the HADS-A score before and after oral administration in each group, the point estimate of the between-group difference, and the 97.5% confidence interval are calculated. Group means are compared using the *t* test. The incidence of postoperative delirium in each group, the point estimate of the between-group difference, and the 97.5% confidence interval are calculated, and the proportions are compared by the chi-square test. Because there are two primary endpoints, Bonferroni adjustment for multiplicity is performed, and a two-sided significance level of 2.5% is used for the two comparisons. If superiority of the Yokukansan group is observed in either of the endpoints, treatment with Yokukansan will be considered to be useful. The interim analysis examined only the Yokukansan group but not both groups, and we do not regard this as a multiple analysis.

Interim analysis will be performed when the number of subjects who have completed the protocol treatment and are evaluable for both endpoints reaches one-third (*n* = 74) of 220, which is the target number of registered patients in this study. At that time, we will determine whether or not continuation of the study is appropriate. If it is determined that the main purpose of the study has not been fulfilled, the study will be discontinued, and the study results will be promptly disclosed. In principle, registration will not be suspended during the interim analysis. When the point estimate of the mean preoperative anxiety score in the Yokukansan group exceeds 5 points or the incidence of postoperative delirium exceeds 40% in the interim analysis, the Independent Data Monitoring Committee, which consists of three external members, will judge whether or not to discontinue the study.

Serious adverse events are described in detail. For other adverse events, the number of subjects with the highest observed grade and the incidence of the highest grade in each treatment group are calculated, and the groups are compared by the Mantel test.

We define the analysis sets as follows. The *full analysis set* consists of all randomized subjects who satisfy eligibility criteria, receive any study drug, participate in at least one postbaseline assessment, and have no Good Clinical Practice (GCP) violations. The *per-protocol set* excludes subjects in which the study is not carried out as per protocol because consent is withdrawn, whose surgery is canceled, who do not take the study drug according to the protocol, etc. The *safety analysis set* includes all subjects who receive any study treatment (including control) but excludes subjects who withdraw prior to receiving any treatment. Data that have been rejected due to missing information, lack of clarity, or faulty handling of data are not included in the analysis. We do not impute the missing data.

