### Study setting and sample

We are conducting our study at the National Cancer Center Hospital, a tertiary hospital for cancer in Japan. We are recruiting patients meeting all of the following inclusion criteria: (1) histologically confirmed malignant tumor or clinically confirmed neoplastic lesion that is speculated to be appropriately treatable by resection; (2) scheduled to undergo highly invasive surgery, defined as tumor resection estimated to last 6 h or longer [39]; (3) Hospital Anxiety and Depression Scale-Anxiety (HADS-A) score of at least 1 at the time of registration; (4) ability to take study drugs orally; and (5) age of 20 years or older.

Exclusion criteria are as follows: (1) diagnosis of delirium based on the Diagnostic and Statistical Manual of Mental Disorders, Fifth Edition (DSM-5) at the time of recruitment; (2) use of any Japanese herbal medicine within 4 weeks before the day of registration; (3) history of allergy to Japanese herbal medicine; and (4) hypokalemia rated as grade 2 or higher according to the Common Terminology Criteria for Adverse Events, fourth version (CTCAE v 4.0) within 8 weeks before the day of registration.

The subject accrual period is from August 2017 to March 2019, and we plan to complete the analysis by March 31, 2021.

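### The primary HADS-A comparison leaves the collected baseline score unused, and its sample size pairs a difference in change with an SD worded as that of the score

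*Protocol article*

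**What the plan says.** The Primary outcomes section of the protocol article defines the anxiety endpoint as the difference between two HADS-A scores, one obtained before the first dose and one on the afternoon before surgery. Statistical analysis then asks for "The mean change in the HADS-A score before and after oral administration in each group, the point estimate of the between-group difference" and its 97.5% confidence interval, and fixes the test: "Group means are compared using the *t* test". No covariate is named.

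The Sample size calculation section puts the effect on the change scale: "we assume a between-group difference in the mean change in preoperative anxiety of 1.5 points". The spread is worded on the score scale: "Assuming a 3-point standard deviation in the preoperative anxiety score". With "a two-sided significance level of 2.5% is used for each endpoint" and 80% power, it concludes that "78 subjects per group are necessary". The delirium endpoint needs 99 per group, and planned registration is 110 per group.

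**The concern.** There are two linked points.

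- **Unused baseline.** A t test on raw change subtracts the baseline with a fixed coefficient of 1, whatever the correlation between the two scores. ANCOVA estimates that coefficient. For correlations below 1 it gives a smaller error variance, using data that the trial already collects.
- **Mixed scales in the sizing.** The numerator is a difference in mean change, but the denominator is described as the SD of a score. The two SDs coincide only at one particular correlation when the SDs before and after dosing are equal, and the article gives neither that correlation nor an SD of change.

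Power for one of two primary endpoints may therefore rest on an unstated quantity. It matters because superiority on either endpoint is enough for the drug to be called effective.

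**Working it through.** **Inputs from Sample size calculation.** Difference 1.5; SD 3; two-sided alpha 0.025; power 80%; 78 per group for anxiety; 99 per group for delirium; 110 per group registered. No dropout rate is given; 110 × 0.9 = 99, so 99 evaluable corresponds to a 10% loss. The correlation r is not stated, so it is an assumption, shown over a range.

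**Step 1: reproduce the 78.** Normal approximation: n = 2 × [3 × (2.2414 + 0.8416) / 1.5]² = 76.04, rounded up to 77. The exact two-sample t calculation (noncentral t) gives 78, with power 80.4%. The stated figure is therefore the t-test size for an analysed variable with SD 3.

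**Step 2: SD of the analysed variable if 3 is the score SD.** With an SD of 3 both before and after dosing:

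- SD of change = 3 × √(2(1 − r)), which equals 3 only at r = 0.5.
- ANCOVA residual SD = 3 × √(1 − r²).
- Variance ratio, ANCOVA to change = (1 − r²) / [2(1 − r)] = (1 + r)/2, which is 0.65 at r = 0.3 and 0.75 at r = 0.5.

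**Step 3: power at the three relevant sizes.** Noncentral t with difference 1.5 and alpha 0.025; the one degree of freedom spent on the covariate is ignored. Power cells show t test on change / ANCOVA.

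| r | SD of change | n per group, change | n per group, ANCOVA | Power, 78 per group | Power, 99 per group | Power, 110 per group |
|---|---|---|---|---|---|---|
| 0.2 | 3.79 | 123 | 75 | 58.2% / 82.1% | 69.9% / 90.8% | 75.0% / 93.6% |
| 0.3 | 3.55 | 108 | 71 | 64.7% / 84.3% | 76.2% / 92.3% | 80.9% / 94.8% |
| 0.4 | 3.29 | 93 | 66 | 72.1% / 87.2% | 82.9% / 94.2% | 87.0% / 96.3% |
| 0.5 | 3.00 | 78 | 59 | 80.4% / 90.9% | 89.5% / 96.4% | 92.6% / 97.8% |
| 0.7 | 2.32 | 47 | 41 | 96.1% / 98.2% | 98.8% / 99.6% | 99.4% / 99.8% |

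**Step 4: break-even correlations for the t test on change.** The largest SD of change that keeps 80% power is 3.013 at 78 per group, 3.401 at 99 and 3.587 at 110. Solving r = 1 − SD²/18 gives about 0.50, 0.36 and 0.29.

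**Step 5: unequal SDs.** Suppose the post-dose SD is 3.5 and the baseline SD is 3.

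- At r = 0.5, the SD of change is √(9 + 12.25 − 10.5) = 3.28, needing about 92 per group. The ANCOVA residual SD is 3.5 × √0.75 = 3.03, needing about 79.
- At r = 0.3, the ANCOVA residual SD is 3.5 × √0.91 = 3.34, and power at 78 per group is 71%. Since 3.34 is below 3.401, 99 per group would still give at least 80%.

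**The case against.** **The trial is larger than 78 per group.** This stands. Delirium drives the size to 99 evaluable and 110 registered, and the Trial status section reports 195 randomised by October 2018. A reader might take the 65% power at r = 0.3 in the 78-per-group column as this trial's power. It is not: the figure at that correlation is 76% with 99 evaluable and 81% with 110.

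**The 3 points may be a loosely worded SD of change.** This also stands. The surrounding sentences concern change, and the figure is attributed to an observational study whose results are not reproduced in the article. If 3 is the SD of change, the 78 matches the planned test exactly. The article does not settle this, so it cannot be called a proven sizing error. The case for baseline adjustment does not depend on the answer, because the variance ratio (1 + r)/2 holds either way under equal SDs.

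**The t test is valid.** Correct. A reader might infer that unstratified randomisation plus regression to the mean biases the comparison. It does not: over randomisation the difference in mean change is unbiased and the type I error is kept, stratified or not. Adjustment gains precision and accounts for whatever chance imbalance is observed.

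**Low baseline scores.** Entry requires only a "Hospital Anxiety and Depression Scale-Anxiety (HADS-A) score of at least 1 at the time of registration", and a patient scoring 1 can improve by at most 1 point. This suggests that the effect may vary with baseline. A single-slope ANCOVA does not model such variation, so the floor adds little to the case for it.

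**ANCOVA is not a guarantee.** A reader might infer that 78 per group is safe under ANCOVA for any non-negative r. That holds only if the post-dose SD is about 3 or less, as Step 5 shows.

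**Conclusion.** The point holds as one of efficiency and clarity, not validity. The planned test is sound but discards precision: under equal SDs, ANCOVA variance is 35% smaller at r = 0.3 and 25% smaller at r = 0.5. If the 3 points is the score SD, as worded, the 78 per group delivers 80% power for the t test on change only at r of about 0.5 or more. At the size actually planned, power is below 80% only for r under about 0.36 (99 evaluable) or 0.29 (110).

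These figures assume a 1.5-point difference, an SD of 3 at both times, two-sided alpha of 2.5%, and values of r that the article does not supply. This is something that should be fixed; it does not endanger the trial's conclusions.

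**What to change.** 1. Before unblinding, amend the primary anxiety analysis to an ANCOVA of the HADS-A score on the day before surgery, with treatment as factor and pre-dose HADS-A as covariate. Report the adjusted difference with its 97.5% confidence interval. Keep the t test on change as a sensitivity analysis.
2. In Sample size calculation, state whether the 3 points is the SD of the score or of the change. If it is the score SD, state the assumed r.
3. Where 78 per group is carried over to the ANCOVA, say that it presumes a post-dose SD of about 3 or less.

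Cost: no new data or patients, and one degree of freedom. It does change a stated primary analysis while the trial is running, so it needs a dated protocol amendment and not only a wording change in the analysis plan. Because the interim analysis looks at outcomes in the Yokukansan group, the amendment should record that it was decided without knowledge of those results or of any between-group comparison.

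### The fixed 2.5% Bonferroni split is valid, but Holm's step-down would give more power for the second of the two efficacy claims at the same 5% familywise error

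*Protocol article*

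**What the plan says.** The Sample size calculation section of the protocol article sets the level: "considering the Bonferroni adjustment for multiplicity, a two-sided significance level of 2.5% is used for each endpoint". The Statistical analysis section applies it to the final tests: "Bonferroni adjustment for multiplicity is performed, and a two-sided significance level of 2.5% is used for the two comparisons". Anxiety is tested with a t test and delirium with a chi-square test, each with a 97.5% confidence interval. Neither section describes a step-down or any passing on of alpha.

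The decision rule appears twice, with the same content: "If the superiority of Yokukansan over placebo for either endpoint is confirmed, the drug would be considered to be effective" and "If superiority of the Yokukansan group is observed in either of the endpoints, treatment with Yokukansan will be considered to be useful".

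The Abstract, the end of the Background and the Study design section name the effect on preoperative anxiety and the prevention of postoperative delirium as two separate efficacy aims.

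**The concern.** The either-endpoint rule settles whether the drug is called useful. It does not settle which of the two effects has been shown, and the stated objectives ask about both. Under the fixed split, suppose anxiety succeeds and delirium gives p = 0.03. The delirium effect is then not claimed, although a procedure with the same 5% familywise control would allow the claim. Delirium is also the endpoint with less power on the planning values, so it is the one more likely to fall between 0.025 and 0.05. What is at stake is the efficiency of the second claim. The validity of the first is not in question.

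**Working it through.** **Inputs** (Sample size calculation section)
- Level: "a two-sided significance level of 2.5% is used for each endpoint"; power 80%.
- Delirium: "we estimated the incidence of delirium at 40% in the placebo group and 20% in the Yokukansan group".
- Anxiety: "a between-group difference in the mean change in preoperative anxiety of 1.5 points", SD 3.
- Required numbers: 99 per group (delirium) and 78 per group (anxiety); planned enrolment 110 per group.
- The correlation between the endpoints is not given. I assume 0 to 0.5.

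**Step 1: reproduce the stated numbers.**
- Delirium, pooled variance, no continuity correction: n = [z(0.9875)·√(2·0.3·0.7) + z(0.80)·√(0.4·0.6 + 0.2·0.8)]² / 0.2² = (2.2414·0.6481 + 0.8416·0.6325)² / 0.04 = 98.5, so 99. This matches the stated figure.
- Anxiety, normal approximation: n = 2·3²·(2.2414 + 0.8416)² / 1.5² = 76.04, so 77. The noncentral t gives power 79.8% at 77 and 80.4% at 78, so 78. This also matches.

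**Step 2: power of each test alone** (pooled chi-square approximation; noncentral t)

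| n per group | Delirium, 2.5% | Delirium, 5% | Anxiety, 2.5% | Anxiety, 5% |
|---|---|---|---|---|
| 99 | 0.8022 | 0.8725 | 0.8950 | 0.9383 |
| 110 | 0.8461 | 0.9046 | 0.9258 | 0.9583 |

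**Step 3: Holm, endpoints independent, 99 per group.** Write D and A for delirium and anxiety power, with the level as subscript.
- Delirium: D₂.₅ + A₂.₅·(D₅ − D₂.₅) = 0.8022 + 0.8950·0.0702 = 0.865.
- Anxiety: A₂.₅ + D₂.₅·(A₅ − A₂.₅) = 0.8950 + 0.8022·0.0432 = 0.930.
- Both, Bonferroni: 0.8022·0.8950 = 0.718.
- Both, Holm: D₅·A₅ − (D₅ − D₂.₅)·(A₅ − A₂.₅) = 0.8186 − 0.0030 = 0.816.
- At least one, either method: 1 − 0.1978·0.1050 = 0.979.

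**Step 4: allow for correlation** (bivariate normal with the powers of Step 2; each range runs from correlation 0 to 0.5)

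| | Bonferroni, n = 99 | Holm, n = 99 | Bonferroni, n = 110 | Holm, n = 110 |
|---|---|---|---|---|
| Delirium | 80.2% | 86.5–85.9% | 84.6% | 90.0–89.5% |
| Anxiety | 89.5% | 93.0–92.0% | 92.6% | 95.3–94.6% |
| Both | 71.8–75.0% | 81.6–83.2% | 78.3–80.7% | 86.5–87.5% |
| At least one | 97.9–94.7% | 97.9–94.7% | 98.9–96.5% | 98.9–96.5% |

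**Step 5: error rates.** With both nulls true, Holm makes a false claim only when its first step rejects. That step is the Bonferroni test, so the familywise error is the same (simulated at 4.9% to 4.7% for correlation 0 to 0.5). With one null true, independent endpoints and 99 per group, the false-claim rate for the null endpoint is 0.025 + 0.025·(power of the other at 2.5%):
- null delirium, anxiety effective: 0.025 + 0.025·0.8950 = 4.7%, against 2.5% under Bonferroni;
- null anxiety, delirium effective: 0.025 + 0.025·0.8022 = 4.5%, against 2.5%.

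Both stay within 5%. Holm guarantees that limit under any dependence.

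**The case against.** The strongest case for leaving the text alone has four parts.

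- **Nothing is wrong.** Bonferroni is valid, and the two sections agree on level, sidedness and success rule. A reader might infer from this point that the multiplicity adjustment is faulty or the sample size wrong. The documents support neither: both stated numbers reproduce at 2.5%. This part stands in full.
- **The stated decision gains nothing.** Success means superiority on either endpoint, and that probability is identical under both methods. A reader might take the rise in power for both claims as a better chance of trial success. It is not, because the protocol neither requires nor powers for winning both. The gain is still real for the second claim, since both effects are stated aims.
- **Holding each endpoint at 2.5% is defensible.** Each endpoint supports its own clinical claim, and under Holm a null endpoint can reach a false-claim rate of 4.5–4.7% when the other works. The 97.5% intervals also match the fixed tests now and would not always match a second-step decision. Both costs are real. The first lies within the 5% overall limit that the protocol accepts; the second can be handled by a reporting rule.
- **It is late.** The Trial status section reports 195 of 220 randomized by October 5, 2018. The Statistical analysis section describes an interim look at the Yokukansan arm, partly in the past tense. A relaxed second test therefore needs a documented justification. That is a condition on the fix, not a reason against it.

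The Background reports delirium in about 32% of patients in the hospital's observational study, against the 40% used for planning. Using the lower rate would make the gain look larger, but that discrepancy is a separate sample-size matter and carries no weight here.

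**Conclusion.** The point holds as an optional efficiency improvement and not as an error. For a trial with two separate efficacy aims, the fixed split gives up power for the second claim that 5% familywise control does not require it to give up. At 99 per group Holm adds about 6 points for delirium and 2 to 3 for anxiety. Power for both claims rises by about 8 to 10 points at 99 per group and 7 to 8 at 110. The chance of at least one win, the familywise limit and the sample size are unchanged. These sizes rest on the protocol's own effect assumptions and on an assumed correlation of 0 to 0.5; the error control rests on neither.

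**What to change.** In the Sample size calculation and Statistical analysis sections, replace the fixed split with Holm's procedure: test the smaller of the two primary p-values at two-sided 2.5% and, only if it is significant, the other at two-sided 5%. Keep the sample-size calculation at 2.5%, since the first step is unchanged.

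State that the Holm decision governs the claim for each endpoint. Report the 95% interval beside the planned 97.5% interval, and warn that a second-step win with p between 0.025 and 0.05 may have a 97.5% interval that includes no effect. Acknowledge that the error rate for a single null endpoint can exceed 2.5% while the familywise rate stays at or below 5%.

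Make the change in a dated amendment before unblinding. It should say whether the Yokukansan-arm interim look had already taken place and confirm that no comparative data informed the change. The cost is a short amendment and one additional interval per endpoint; no further patients or data are needed.
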